## Methods

### Aims and outcomes

The aim of this study is to determine whether antihypertensive medications can be safely reduced without systolic blood pressure increasing beyond what is clinical acceptable at follow-up.

The primary outcome is the proportion of participants with clinically acceptable blood pressure levels at 12-week follow-up (defined as a systolic blood pressure <150 mm Hg). Secondary outcomes will examine:The proportion of participants in the intervention arm who maintain medication reduction through to follow-up (ie, are *not* restarted on therapy).The difference in quality of life (according to EQ-5D-5L) between groups at 12-week follow-up.The difference in frailty (according to the frailty index)^22^ between the two groups at 12-week follow-up.The difference in the change in mean clinic systolic blood pressure (from baseline) between the two groups at 12-week follow-up.The difference in reported side effects to medication between the two groups at 12-week follow-up (including coughs, dizziness, syncope, and ankle swelling).The difference in routinely reported serious adverse events (SAEs) between the two groups at 12-week follow-up (hospitalisation due to falls, myocardial infarction, stroke or all-cause mortality).

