### Baseline visit

Eligible patients will have informed consent taken by the GP. During the consent appointment, the GP will show a 2 min study video infographic (see online supplementary material) and go through the participant information sheet explaining the exact nature of the trial. Having had a chance to ask questions, those individuals willing to participate will give written informed consent by means of a participant dated signature and dated signature of the GP who presented and obtained the informed consent.

10.1136/bmjopen-2018-022930.supp1Supplementary data

Some participants will be invited to have their interview audio-recorded for qualitative analysis during their study visits. Those who are interested will be asked to sign a response slip prior to meeting the GP. Consent to audio-recordings will not have a bearing on an individual’s care or eligibility for the main trial.

Those giving informed consent will be screened using the criteria in box 1 and undergo baseline measurements and randomisation by a member of the research team via participant questionnaires and a detailed notes review (table 1).

**Table 1 T1:** Variables and schedule of data collection

No.	Variable	Data source		Schedule	
		Medical notes	Measured/collected at clinic	Baseline	Follow-up
1	Age		✓	✓	
2	Sex		✓	✓	
3	Ethnicity		✓	✓	
4	Marital status		✓	✓	
5	Education		✓	✓	
6	Duration of hypertension	✓		✓	
7	Past medical history	✓		✓	
8	Alcohol consumption		✓	✓	✓
9	Smoking		✓	✓	✓
10	Height		✓	✓	✓
11	Weight		✓	✓	✓
12	Clinic blood pressure (sitting and standing)		✓	✓	✓
13	Cholesterol (total and HDL)	✓		✓	
14	Estimated glomerular filtration rate	✓		✓	
15	Prescribed or over-the-counter medications (all medications)*	✓	✓	✓	✓
16	Quality of life (according to EQ-5D-5L)^26^		✓	✓	✓
17	Functional independence (defined by modified Rankin Scale)^38^		✓	✓	
18	Frailty (according to the FRAIL scale)^39^		✓	✓	✓
19	Frailty (according to the frailty index and electronic frailty index)^22 40^	✓	✓	✓	✓
20	Cognitive function (defined by the Montreal Cognitive Assessment)^41^		✓	✓	
21	Adherence to medication (according to the Medication Adherence Rating Scale Questionnaire)^42^		✓	✓	✓
22	Adherence to medication reduction		✓		✓
23	ICD-10 coded cardiovascular events and mortality during the trial	✓			✓
24	Recording of potential side effects to medication		✓	✓	✓
25	Recording of adverse events	✓	✓		✓

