### Randomisation

Consenting participants will be individually randomised (1:1 allocation ratio) to one of two study arms using a fully validated web-based system (Sortition) with manual telephone back up. Participants will not be randomised until after consent has been taken and baseline assessments have been completed. A computer-generated non-deterministic algorithm, minimising on practice and baseline systolic blood pressure will be used to ensure these covariates are balanced between the two intervention arms.

The study will use an open-label design, so patients and practitioners will not be blinded to the intervention or study end points. Therefore, codebreaking will not be necessary. The statistical analysis will be performed blind to patient allocation.

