### Statistical analysis

A detailed statistical analysis plan will be agreed prior to the end of the trial. The primary and secondary analyses will be by intention to treat (ITT), unless stated otherwise. The primary analysis will be a non-inferiority analysis by means of the ‘two one-sided test’ procedure,^32^ whereby the 95% CI for the relative risk of participants with systolic blood pressure at 12 weeks below 150 mm Hg between the medication reduction group and the usual care group is calculated. This will be obtained by means of a generalised linear mixed effects model with GP surgery included as a random effect and baseline blood pressure as a fixed effect. If the lower limit of the CI is >0.9 (equal to a risk difference of 10%) then the research hypothesis that medication reduction will be non-inferior in terms of blood pressure control to usual care will be accepted. As a secondary analysis of the primary outcome, a per-protocol (PP) analysis will be performed, since ITT can be anticonservative for a non-inferiority hypothesis.^32^ Participants who received the medication reduction intervention in the PP analysis will be defined as a participant in the medication reduction arm who maintained their medication reduction throughout the 12-week follow-up period.

Secondary analyses will examine the proportion of participants in the medication reduction arm who maintained their medication reduction throughout the 12-week follow-up period. Secondary outcomes will be analysed by means of linear mixed effects models, adjusting for the baseline level of the outcome and baseline systolic blood pressure and including practice as a random effect: systolic blood pressure, EQ-5D-5L and the Frailty index/frail scale. The difference in the rate of side effects and AEs between the medication reduction and usual care arms will be analysed by means of a logistic mixed effects model adjusting for baseline systolic blood pressure and including practice as a random effect.

Exploratory subgroup analyses of blood pressure control, change in blood pressure and maintenance of medication reduction will be conducted by different levels of baseline frailty, functional independence, cognitive function, number of medications prescribed at baseline and number of comorbidities at baseline.

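### The side-effect model omits the baseline status of the side effect, which Table 1 collects: the comparison stays valid but gives up precision

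*Protocol article*

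**What the plan says.** The Statistical analysis section gives side effects and adverse events (AEs) one shared model, "analysed by means of a logistic mixed effects model adjusting for baseline systolic blood pressure and including practice as a random effect". The sentence before it analyses systolic pressure, EQ-5D-5L and frailty with linear mixed models "adjusting for the baseline level of the outcome and baseline systolic blood pressure and including practice as a random effect". The two sentences therefore list different covariates: the baseline level of the outcome is in one and not in the other.

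Table 1 (Baseline visit) separates the two outcomes that share the logistic model. Row 24, "Recording of potential side effects to medication", is ticked at baseline and at follow-up. Row 25, "Recording of adverse events", is ticked at follow-up only.

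The outcome, in Aims and outcomes, is "The difference in reported side effects to medication between the two groups at 12-week follow-up", with cough, dizziness, syncope and ankle swelling as examples. Allocation uses an algorithm "minimising on practice and baseline systolic blood pressure" (Randomisation), so baseline symptoms are not balanced by design. The analysis section also announces a detailed analysis plan to follow, and the strengths and limitations box says that the trial is not necessarily powered for secondary outcomes.

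**The concern.** Participants enter on two or more antihypertensives, and some will already report the symptoms that are counted again at week 12. If a symptom tends to persist, its presence at baseline carries information about its presence at follow-up. Leaving it out of the model has two costs. The variation it explains stays in the comparison, so power is lower than the data allow. And if one arm starts with more symptomatic participants by chance, that difference passes partly into the 12-week comparison with nothing to correct it.

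The article applies the usual remedy to the continuous outcomes, and the data needed to apply it here are already collected. Side effects are a listed secondary outcome for which power may be limited, so precision should not be given up without a reason.

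**Working it through.** **Inputs from the article.** Total 540; 10% loss to follow-up; 1:1 allocation; side effects recorded at baseline and follow-up; minimisation on practice and systolic pressure. Analysed number: 540 × 0.9 = 486, or n = 243 per arm.

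**Inputs assumed, because the article gives none.** Symptom prevalence p of 20% and 40% (30% for one illustration); odds ratio (OR) between baseline and follow-up presence of 1, 3, 10 and 20.

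**The plan's own figure.** No figure is stated for the side-effect comparison. The total of 540 for the primary outcome does reproduce: the Farrington-Manning method with 100% v 96%, a 10-point margin, 90% power and one-sided 2.5% gives 196 per arm. Dividing by 0.9 for loss and by 0.9² for dilution gives 196 / 0.729 ≈ 269 per arm, 538 in total. The base of 243 per arm is therefore sound.

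**Chance imbalance at baseline.** SE = √(2p(1 − p)/n).
- p = 20%: √(0.32/243) = 3.6 points
- p = 30%: √(0.42/243) = 4.2 points
- p = 40%: √(0.48/243) = 4.4 points

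**How much passes into the 12-week comparison.** Let q0 be the follow-up risk in those without the symptom at baseline and q1 the risk in those with it. Both are fixed by the OR and by (1 − p)q0 + p·q1 = p, so that control-arm prevalence stays constant. A baseline imbalance d shifts the unadjusted 12-week difference by (q1 − q0)·d. The table takes d = 2 SE.

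| p | OR | q0 | q1 | q1 − q0 | Shift, points |
|---|---|---|---|---|---|
| 20% | 3 | 16% | 36% | 0.20 | 1.5 |
| 20% | 10 | 11% | 56% | 0.44 | 3.2 |
| 20% | 20 | 9% | 65% | 0.57 | 4.1 |
| 40% | 3 | 30% | 56% | 0.26 | 2.3 |
| 40% | 10 | 19% | 71% | 0.51 | 4.6 |
| 40% | 20 | 15% | 78% | 0.63 | 5.6 |

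**Power.** Simulation with 243 per arm, 3,000 trials per setting, two-sided 5%, logistic regression with and without the baseline symptom. The effect was set to give about 80% power unadjusted (20% reduced to 10.8%; 40% reduced to 28.0%). Practice and systolic pressure terms were left out. Monte Carlo error of each power is about √(0.8 × 0.2/3000) = 0.7 points.

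| p | OR | Without term | With term | Gain, points |
|---|---|---|---|---|
| 20% | 1 | 79.5% | 79.6% | 0.1 |
| 20% | 3 | 79.4% | 80.4% | 1.0 |
| 20% | 10 | 81.5% | 88.6% | 7.1 |
| 20% | 20 | 78.9% | 90.6% | 11.7 |
| 40% | 1 | 79.8% | 80.0% | 0.2 |
| 40% | 3 | 79.7% | 82.2% | 2.5 |
| 40% | 10 | 79.7% | 89.1% | 9.4 |
| 40% | 20 | 81.0% | 93.6% | 12.6 |

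**Type I error.** Over all simulated null trials it is 4.3% to 5.2% without the term and 4.6% to 5.5% with it. Among null trials whose baseline imbalance was at least 1.5 SE (328 to 406 of 3,000), it is 6% to 8% without the term at OR 3, 13% to 14% at OR 10 and 17% to 20% at OR 20, against about 3% to 7% with it.

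**The case against.** **The planned analysis is not wrong.** It adjusts for both minimisation factors, and randomisation keeps the error rate at its nominal level. This stands. A reader might infer from the conditional error rates that the comparison is biased. They apply only to samples that happen to be imbalanced, and the overall rate is near 5%.

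**The outcome is not change.** A reader might say that without the baseline value the model fails to address change in side effects. Aims and outcomes defines a difference between groups at 12 weeks, and uses the word change only for systolic pressure. The case for the covariate is precision and imbalance, not a different outcome.

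**The strength of the association is unknown.** It is tempting to call baseline status the strongest predictor, or relief of side effects the main expected benefit of reduction. The article says neither. Persistence is plausible for cough or ankle swelling, less so for syncope, which is episodic. Larger gains can be obtained, but only from strong assumptions. With 30% prevalence, 80% persistence, 8% new onset and a conditional treatment OR of 0.6, power rises from 24% to a little over 40%, but that pair implies an association OR of (0.80/0.20)/(0.08/0.92) = 46. With 65% and 12% it is 13.6.

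**The sentence is condensed, and an analysis plan is to follow.** It covers AEs too, which have no baseline value, so it may list only the shared covariates. That may explain the wording. It does not remove the point, because the covariates are stated, they differ from those in the preceding sentence, and a later plan built on this text would inherit the omission.

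**The term has a small price.** The logistic odds ratio is non-collapsible, so the estimate becomes conditional on baseline status, and a sparse indicator can be unstable in a mixed model. Both stand and shape the fix.

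**Conclusion.** The point holds as a loss of precision in a valid secondary analysis. The stated side-effect model leaves out a baseline measure that is collected, departs without explanation from the rule used for the continuous outcomes, and has no balance by design to fall back on.

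The size depends on an association that the article does not give. The gain is negligible if baseline and follow-up symptoms are unrelated, about 1 to 3 points of power at an OR of 3, and about 7 to 13 points at ORs of 10 to 20. A two-SE baseline imbalance would move the 12-week difference by 1.5 to 5.6 points over ORs of 3 to 20. These figures assume 243 analysed per arm, prevalence of 20% to 40% and no practice or systolic pressure effects in the simulation. Neither an invalid test nor a uniformly large gain is supported.

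**What to change.** In each side-effect model, add presence of the same side effect at baseline as a fixed effect, alongside baseline systolic pressure and the practice random effect, where events are frequent enough to estimate it. State in advance what is done when they are not, for example that the term is dropped for rare symptoms such as syncope. Say that the odds ratio is then conditional on baseline status. Leave the AE model as planned, and describe the two models in separate sentences. If the omission is deliberate, give the reason.

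The change needs no new data and no larger sample. Its cost is one pre-specified covariate, a conditional odds ratio to interpret, and possible instability for rare symptoms. It should be fixed before outcome data are compared by arm.

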### Safety reporting

AEs that are observed by an investigator or reported by the participant will be recorded on the AE log at any time during the study but AEs will be specifically asked about at the 12-week follow-up. SAEs will be reported to the coordinating centre within 24 hours of discovery or notification of the event. All SAE reports will be reviewed by the DMEC chair on a monthly basis, and by the full DMEC at meetings held every 6 months. The DMEC will include a geriatrician, statistician and consultant clinical pharmacologist. They will be responsible for safeguarding trial participants, monitoring emerging trial data including identifying any trends, such as increases in unexpected events, and take appropriate action where necessary.

All AEs labelled possibly, probably or definitely related will be considered as related to the intervention. Since there are no sections of the Summary of medicinal Product Characteristics, or previous clinical studies which detail expected AEs as a result of medication withdrawal, all SAEs at least possibly related, and not as a result of re-introduction of withdrawn medication, will be considered unexpected and reported as Suspected Unexpected Serious Adverse Reaction (SUSARs). Fatal and life-threatening SUSARs will be reported by the chief investigator to the relevant Competent Authority and Research Ethics Committee no later than 7 calendar days after the sponsor or delegate is first aware of the reaction. All other SUSARs will be reported within 15 calendar days.

### Qualitative substudies

#### Study 1: interviews with doctors and patients

Face-to-face interviews with GPs and patients will be conducted to generate understanding about the barriers and facilitators to antihypertensive medication reduction. Informed consent will be sought from approximately 15 GPs to provide a broad range of opinion from varying practice sizes (small to large) and settings (rural to urban). Participating GPs will also be asked to identify up to 15 patients for interview, based on the same inclusion criteria as those applied to participants in the main trial.

Interviews with GPs will use a chart-stimulated recall approach to explore the factors which influence their treatment choices in older hypertensive patients. Anonymised electronic health records will be used to focus discussions about how GPs would feel about reducing antihypertensive medications. Interviews with patients will use ‘brown bag’ medication review techniques^33^ to create a complete record of medication held, with a commentary on usage from the participants’ perspective. Diagrammatic elicitation techniques will be used to complete a relational map outlining participants’ circumstances and how these relate to the medications taken. These sketches will be used as the basis for a discussion on the implications of withdrawing antihypertensive medications, and what this ‘gap’ might mean for the patient.

All interviews will be transcribed verbatim, stored and organised using NVivo software (QSR International, Doncaster, Victoria, Australia). Interview and visual data from GP and patient interviews will be subjected to thematic analysis, with a particular orientation to exploring clinical and patient perspectives on the barriers and facilitators to reducing antihypertensives.

#### Study 2: assessment of trial recruitment and data collection procedures

The aim of the second qualitative study will be to explore how information is presented within recruitment appointments and how this might impact on consent to participate, with a view to ensuring robust trial procedures using an iterative process. This will be achieved by audio-recording (with consent) up to 75 consultations between GPs or research assistants and eligible patients.

Thematic analysis will be undertaken on a sample of around 15–20 consultations comprising patients who did, or did not consent to participate, to consider (a) terminology used, (b) presentation of the deprescribing approach and (c) presentation of randomisation. This will inform ongoing trial procedures and future implementation.

### Economic substudy

This work will adapt a previous decision-analytic model examining the long-term costs and benefits from blood pressure-lowering treatment^34^ to include potential harms of treatment. The model will be adjusted for the effects of blood pressure lowering on cardiovascular disease risk, costs and quality-adjusted life-years (QALYs) to match the older population involved in this work. Costs of the therapies prescribed, side effects and acute and long-term costs of cardiovascular events will be obtained within the trial and from the literature. Quality of life on each treatment strategy will be obtained from the trial data using EQ-5D-5L, and previous studies will inform utility values for cardiovascular disease health states and the impact of side effects. The model will determine the cost per additional QALY gained of the medication reduction intervention versus usual care and analyses will be conducted from a health and social services perspective. The model will be run with a lifetime perspective, with costs and benefits discounted at a rate of 3.5%. A value of information analysis will assess whether a further trial would be appropriate to reduce decision uncertainty, and identify those parameters where more precise estimates would be most valuable and should therefore be chosen as outcomes for such a trial.

### Ethics and dissemination

This research involves older participants, some of whom may be considered vulnerable. Great care will be taken to ensure all potential participants have the trial clearly explained, and are given sufficient time to decide whether to give informed consent. This will include provision of simplified, participant information sheets with large fonts, video infographics to explain the study and extended GP consultation periods for explaining the study and taking informed consent. The study sponsor has reviewed the study proceedures and ensured all indemnity and insurance requirements for the trial were in place prior to the start of recruitment.

All research outputs from this work will be published in peer-reviewed journals, presented at scientific conferences and lay and social media (eg, Twitter, blogs). ‘Patient friendly’ study summary documents and infographics will be made available to all participants at the end of the trial via the study website.

### Current trial status

The trial commenced recruitment on 10 April 2017 and is estimated to continue recruitment until September 2018.

## Discussion

Current guidelines in the UK suggest that doctors should ensure that patients are fully informed of the benefits and risks of their prescribed medications and where appropriate, discuss the potential for medication withdrawal in frail individuals with multimorbidity.^35^ This is difficult given consultation time constraints and fear that deprescribing might result in harm.^36^ This is compounded by conflicting and inconclusive evidence about the benefits and harms of treatment, and a lack of evidence about what will happen if these treatments are reduced.

The ECSTATIC trial enrolled 1067 younger participants aged 40–70 years, taking antihypertensives for primary prevention of cardiovascular disease.^18^ The trial demonstrated that only 27% of participants were able to maintain medication reduction throughout follow-up and at 3 months, systolic blood pressure was on average 6 mm Hg higher in the deprescribing group. At 2-year follow-up, the risk of uncontrolled blood pressure was significantly higher in those patients attempting to deprescribe. Unlike the present study, the medication reduction algorithm used did not encourage reintroduction of therapy if blood pressure was persistently raised.

The Discontinuation of Antihypertensive Treatment in Elderly people (DANTE) study^16^ examined the effect of complete antihypertensive medication discontinuation in 385 patients over the age of 75 years and with mild cognitive deficits. After 16 weeks of follow-up, they observed a 7/3 mm Hg increase in blood pressure but no difference in overall cognition compound score or quality of life between groups. A study by van der Wardt *et al*
19 examined the feasibility of a trial reducing antihypertensives in patients with dementia, but was only able to recruit nine participants for the withdrawal programme (1% recruitment rate) and a larger trial was deemed unfeasible. Similarly, the Opti-Med trial^37^ demonstrated in 95 participants that a broader deprescribing approach is achievable in patients living in nursing homes, but was unable to examine the effect on clinical outcomes due to recruitment issues resulting in only 38% of the planned sample size being enrolled.

The OPtimising Treatment for MIld Systolic hypertension in the Elderly (OPTiMISE) trial will target frail individuals with polypharmacy and comorbidity, and aim to establish whether a strategy of antihypertensive medication reduction is safe and acceptable to older patients. The findings of this trial will support better patient-centred management plans for the prevention of cardiovascular disease in older individuals and inform future deprescribing trials in primary care.
